## Abstract

A high consumption of sugar-rich discretionary food and drinks has several health implications, which have been traced from childhood into adulthood. Parents act as primary mediators shaping children’s dietary habits, and interventions that engage parents have shown to result in positive outcomes. Further, collaboration with local school health nurses and dentists provides an effective structural frame to support behaviour change and anchor new initiatives. The multicomponent 3.5-month cluster randomised family-focused intervention “Are you too Sweet?” aims to evaluate the effectiveness of communicating new Danish guidelines for sugar-rich discretionary food and drinks for school starters (5–7 years). This paper describes the development, outcomes and process evaluation of the intervention that includes three main components: extended dialogue during a school health nurse consultation, a box with home-use materials, and a social media platform to facilitate interaction among participants. Children (*n* = 160) and their parents were scheduled for a baseline interview at six different schools. The intervention was developed to increase self-efficacy, knowledge about guidelines, observational learning and reduce impediments for behavioural change. The desired primary outcome was a reduction in intake of sugar-rich food measured through a 7-day dietary record. The results contribute to the evidence on effective health promotion strategies.

## 1. Introduction

A high intake of sugar-rich food and sugar-sweetened beverages (SSB) in children has several health implications. Evidence supports the association between a high intake of SSB and the risk of overweight in children and adults [1,2,3,4,5,6]. A Swedish cross-sectional study among adults suggested that the higher the intake of added sugar in the diet, the more likely it is that the intake of micronutrients will be compromised [7]. Studies from both Denmark and Norway have shown lower intake of dietary fibre, vitamin E, vitamin D, and iron in children with the highest sugar intake compared with children with the lowest intake [8,9]. Likewise data from the UK National Diet and Nutrition Survey 2008–2012 have shown that children with an intake of free sugars above 13% of total energy (E%) had a lower intake of micronutrients compared with children with a lower intake [10]. An Australian study reported that children whose intake of free sugars exceeded 20 E% to be more likely to have inadequate micronutrient intake [11]. Finally, strong evidence supports that sugar intake contributes to the development of dental caries [12,13].

Based on the recognition that the negative health effects, especially dental caries, are cumulative, tracking from childhood to adulthood, the World Health Organization (WHO) recommends reducing the intake of free sugars throughout the life course and lowering the intake of free sugars to less than 10 E%, and preferably to less than 5 E% [14]. The Nordic Nutrition Recommendations (NNR) also advises consuming a diet with less than 10 E% from added sugar [15]. The US Scientific Report of the 2020 Dietary Guidelines suggests a recommendation <6 E%, since they suggests *“[…] that less than 6 percent of energy from added sugars is more consistent with a dietary pattern that is nutritionally adequate, while avoiding excess energy intake from added sugars, than is a pattern with less than 10 percent energy from added sugars.”* [5]. Compared to added sugar, the term free sugar include also sugars naturally present in honey, syrups fruit juice concentrates, which typically is not included in added sugar [5,15,16]

Intake of added sugar mostly comes from “discretionary food”, a term used to define energy-dense but nutrient-poor foods, such as SSBs, pastries, cakes, sweets, chocolate, ice cream, or salty snacks [17]. A Danish qualitative study showed that although parents are well aware of the consequences of eating large amounts of discretionary food, there is great uncertainty as to how much discretionary food is too much [18]. Further, there is great variation between intake of discretionary food during weekdays and weekends, with an intake during weekends exceeding recommendations substantially, i.e., an intake of 14 E% added sugar on average for 4–13 year-old Danish children on Friday and Saturday [19].

Children’s high consumption of discretionary food and drinks [16,20,21,22], with the increased risk of establishing unhealthy habits throughout life, call for sustainable prevention strategies. Several systematic reviews have evaluated the effectiveness of interventions to reduce consumption of discretionary food, especially SSBs, both targeting environmental changes and behavioural changes [13,23,24,25]. Notably, home-based environmental interventions with inclusion of parents have proven to be efficient [23]. However, interventions on reducing sugar-rich discretionary food using theoretical-based family-centred approaches have been limited. Social cognitive theory (SCT) provides a suitable guide for behavioural change in families, with a focus on strengthened self-efficacy through reciprocal determinism, the interaction between humans and environment, and observational learning.

Most European countries have implemented a form of school health service to provide school children with various types of healthcare [26]. In Denmark, children enter the school system into “pre-school class” around the age of six. During this first year, all children together with their parents are invited to a health consultation at the school with the school health nurse. This consultation evolves around communicating both wellbeing and health, and offers an opportunity to communicate guidelines on diet, physical activity, screen time and sleep. The intervention “Are you too Sweet?” aims at using this setting to deliver newly developed guidelines on discretionary food and drinks, and to share several materials developed based on SCT, to engage families to change habits related to discretionary food and drinks. “Are you too Sweet?” involves collaboration with both the school health nurses, the dentist care, and communication partners. This paper describes the development of the components and the study protocol of the multicomponent family-based “real-life” cluster-randomised intervention “Are you to Sweet?” evaluating the feasibility and effectiveness of different strategies for changing the family sugar culture and reducing the intake of sugar-rich discretionary food and drinks among young schoolchildren aged 5–7 years.

## 2. Materials and Methods

### 2.1. The Municipality Setting

In Denmark, primary health prevention in children is part of the local school health nurse’s domain, managed by municipalities. When children are enrolled in the school system, school health nurses consult the families at the school. New national guidelines for schoolchildren, and strategies to communicate these, would have to be adopted at the municipality level. The intervention “Are you too Sweet?” will be performed in the Danish municipality Hvidovre. This municipality is chosen as it represents the national mean for socio-economic status, ethnicity, and education level [27].

### 2.2. Study Design and Setting

“Are you too Sweet?” is a two-arm, parallel, cluster-randomised controlled trial with clusters defined as schools within the municipality. The study investigates the effectiveness of a 3.5-month multicomponent family-based intervention against a control group receiving standard care by the school health nurses. The intervention involves school starters 5–7 years and their parents, in a Danish municipality (Hvidovre), focusing on reducing intake of sugar-rich discretionary food and drinks. Baseline measures will run from October until December 2020, and follow-up measures will run from February until March 2021. Overall, the intervention will consist of a parent performed registration of the child’s intake of discretionary food and drinks, a focused health consultation with the school health nurse, a box with materials and tools to be used at home handed out by the school nurses and finally a social media platform for interaction between participating parents. A flow of the intervention is shown in Figure 1.

#### 2.2.1. Study Population and Sample Size

Eligible children are children starting public pre-school education at six chosen schools in Hvidovre municipality in August 2020. There is no inclusion criteria regarding diet or disease. Power calculations were performed based on 6–7 year-old children from the Danish National Survey of Diet and Physical Activity [28]. Calculations determined that 76 participants will be needed in both intervention and control groups to detect a 25% reduction in the intake of sugar-rich discretionary foods at a power of 80% and a 95% confidence interval. For a 25% reduction in intake of added sugar, 63 participants will be needed. To account for dropouts or loss of participants to follow-up, an enrolment of a minimum of 100 families in the intervention group and an additional 100 families in the control group was planned.

#### 2.2.2. Recruitment and Randomisation

Participants were recruited during the period of March–May 2020. The local dental clinician phoned parents of children starting school in the districts of the six schools in 2020 and asked if they were interested in participating in the intervention. Beforehand, the participants had received the participant information sheet via their personal digital post-box. In total, 237 parents, corresponding to 54% of children starting at the six local schools in Hvidovre, initially accepted to participate. The most common reason for declining participation was lack of time and/or resources. The parents were then contacted again after the start of school, and 160 children and their parents ended up scheduling an appointment at baseline.

Cluster randomisation of schools took place after the recruitment was completed, and children were assigned to the control or intervention group according to randomization of their school. For an even distribution between the control and intervention group, the schools were randomised by the number of children at each school and the schools’ socioeconomic index, using R statistical software package, version 4.0. Information about the individual schools’ socioeconomic index was obtained from the municipality’s school division. For practical reasons, randomisation had to be completed before baseline, and therefore could not be blinded for the investigators. Randomisation was blinded to the participants until after they completed a 7-day dietary record at baseline. An unexpected large dropout rate prior to baseline measures created partly by COVID-19 related disruptions caused concern on the sample size. Thus, based on the initial randomisation parameters (number of children and socioeconomic index), one control school was changed to an intervention school in order to secure statistical power in the intervention group. The distribution between intervention (*n* = 4) and control schools (*n* = 2) is thus unbalanced, however, smaller control groups in public health intervention studies have been shown to be valid previously [29].

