### 2.7. Statistical Considerations

Primary analysis will focus on testing the effectiveness of the intervention, by analysing the change in intake discretionary food and drinks from baseline to the 3.5-month follow-up between intervention and control groups. Changes in intake of discretionary foods and drinks will be expressed in absolute changes (kJ/d) and in relative changes as kJ/10 MJ. Changes in food groups and sub-groups (e.g., chocolate, cakes or ice-cream), will also be evaluated in g/d.

Linear mixed models will be used with discretionary food and drinks as a combined variable, and sugar-rich discretionary food and discretionary drinks separately as outcome variables. Group (intervention or control) baseline intake of discretionary food and discretionary drinks will be analysed as a fixed effect and school as a random effect as there has been a cluster randomisation on school level. Primary outcome will be calculated using intention-to-treat analysis, including all participants irrespective of adherence or dropouts. Missing data will be imputed using multiple imputation. Sensitivity analysis will be performed with complete case analysis, and per protocol analysis, where analysis will be carried out for participants that (1) complete the sugar-rich food screener and health consultation; (2) report to play the card game and used at least one other item from the box. Further, sensitivity analysis will likewise be used to test the effect of having twins or triplets in the intervention.

Adjustment for group imbalances and potential confounders such as parental education, BMI and physical activity will be performed for both primary and secondary outcomes. Estimates of the effect size will be presented along with 95% confidence intervals and p-values. The significance level is set at 5%. Statistical analysis will be carried out using R version 4.0.

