A strength of this intervention is that the school health nurses are highly experienced in anchoring health initiatives and engaged with parents in shaping healthy habits. Further, joining multiple output data on food intake, anthropometry and a range of behaviour change mediators is a strength of our study design, as hypothetical mechanisms of behavioural change will be discussed. On the contrary, analysis of each mediator might be constrained due to low power. A rather large dropout due to delay caused by the novel COVID-19 virus, has weakened the power, resulting in a change to the study design. Therefore, the randomisation has not been optimal, as one school had to be changed from control school to intervention school [29], and that randomisation had to be performed before baseline measures. The COVID-19 situation might influence peoples eating habits as they stay more at home, and school afternoon snacks are not available, but have to be bought from home. The schools included in this project, do not plan to participate in other health related projects related to the COVID-19 situation.

Further, the allocation status could not be blinded, for obvious practical reasons, for participants or those delivering the interventions. However, randomisation was blinded to the participants until after they completed a 7-day dietary record at baseline. In contrast, a strength is that using current school health services has facilitated that families with different socio-economic backgrounds have been enrolled in the intervention. That said, the representativeness of the study might be reduced because some parents declining to participate, as they reported a lack of sufficient resources to fill out the dietary record and survey. The representativeness will therefore be compared with local data of education and ethnicity when data collection is finished.

The pilot study indicated that the measurement procedures and logistics of the intervention is feasible. However, the pilot study had several weaknesses. Some families had too little time to use and test all materials provided by the project due to the short period. The intervention therefore commenced with only minor changes.

This paper has thoroughly described the development of all components used in the intervention in order to ensure a critical evaluation of all components afterwards. Further, statistical considerations have been described in order to avoid data driven analysis.

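### One control school was switched to intervention after randomisation, but the primary analysis is still called intention-to-treat, does not name the allocation it uses, and rests on an unsound power rationale

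*Protocol article*

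**What the plan says.** Section 2.2 of the protocol article describes a "two-arm, parallel, cluster-randomised controlled trial with clusters defined as schools within the municipality". Six schools took part. Section 2.2.1 gives the size requirement: "76 participants will be needed in both intervention and control groups to detect a 25% reduction in the intake of sugar-rich discretionary foods". The settings are 80% power and 95% confidence, and the plan is to enrol at least 100 families per group.

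Section 2.2.2 gives the order of events. Recruitment came first, with 237 initial acceptances. Schools were then randomised with regard to number of children and socioeconomic index. This happened before baseline and was not blinded to the investigators. Participants were kept unaware of allocation until the baseline diet record was complete. Only 160 families went on to book a baseline appointment. Because of the dropout, "one control school was changed to an intervention school in order to secure statistical power in the intervention group". The section says the switch drew on the same two parameters as the randomisation, and it ends with four intervention and two control schools.

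Section 2.7 states: "Primary outcome will be calculated using intention-to-treat analysis, including all participants irrespective of adherence or dropouts". School is a random effect. The sensitivity analyses listed are complete case, per protocol, and the effect of twins or triplets. The Discussion concedes that the randomisation was not optimal, since "one school had to be changed from control school to intervention school".

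**The concern.** Intention-to-treat means analysis in the arm that randomisation assigned. Section 2.7 defines it only by adherence and dropout and does not say whether the moved school counts in its randomised or its changed arm. The 4 v 2 description suggests the changed arm. In that case one of six clusters, and one of four intervention schools, enters the primary comparison through a decision made after the allocation was known. If that school differs from the others in dropout, family background or engagement, the estimate can be biased, and the intention-to-treat label would tell readers that randomisation protects against this. With so few clusters, one school can carry real weight in the result.

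The stated reason is a separate problem. Power is a property of the contrast between arms. Enlarging one arm by shrinking the other does not secure it in general, and the plan's own calculation sets the same requirement for both groups.

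**Working it through.** **1. Allocation.** Four intervention and two control schools after one switch imply three and three before it. The moved school was therefore one of three controls. Section 2.2.2 names two criteria for the switch and describes no random draw. Set beside Section 2.7, an analysis at 4 v 2 is not an analysis by randomised arm for that school.

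**2. The plan's sample size.** Mean and SD are not given; the article says only that "Power calculations were performed based on 6–7 year-old children from the Danish National Survey of Diet and Physical Activity". The figure of 76 cannot be reproduced independently, so I solved it backwards with the normal approximation at two-sided 5% and 80% power:

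d = (1.960 + 0.842) × √(2/76) = 0.454

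For a 25% reduction this implies a coefficient of variation of 0.25/0.454 = 0.55. The t distribution gives d = 0.457, which does not alter the conclusions. Enrolling 100 to keep 76 implies an allowance of 1 − 76/100 = 24%. Loss before baseline was (237 − 160)/237 = 32%.

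**3. Power by split, clustering ignored.** Power = Φ(d/√(1/n₁ + 1/n₂) − 1.96), with 160 children in total. Arm sizes are assumptions, because school sizes are not given.

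| Case | Before switch (int:ctrl) | Power | After switch | Power |
|---|---|---|---|---|
| Equal schools | 80:80 | 82.0% | 107:53 | 77% |
| Small original intervention arm | 60:100 | 79.5% | 87:73 | 81.7% |
| Smaller still | 55:105 | 78.0% | 80:80 | 82.0% |

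At 160 children, 80% power needs at least 63 in the smaller arm (97:63 gives 80.2%). Equal schools leave about 53 in control, below both 63 and the plan's 76.

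**4. After loss.** Applying the implied 24% to the 160 (an assumption about where the allowance applies) leaves 160 × 0.76 = 121.6 children. An even split gives 70.7%, the highest of any split; 2:1 gives 65.6%.

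**5. With clustering.** The article gives no ICC; the values here are assumed. For equal schools of size m, the variance of the difference is proportional to [ICC + (1 − ICC)/m] × (1/k₁ + 1/k₂). From 3:3 to 4:2 it changes by (1/4 + 1/2)/(1/3 + 1/3) = 1.125, a rise of 12.5% at any ICC. At 160 children:

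| ICC | 3:3 normal | 4:2 normal | 3:3, t on 4 df | 4:2, t on 4 df |
|---|---|---|---|---|
| 0.01 | 72.7% | 67.6% | 49.6% | 45.3% |
| 0.02 | 64.7% | 59.6% | 43.0% | 39.2% |
| 0.05 | 47.7% | 43.4% | 31.0% | 28.2% |

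With unequal schools the direction can reverse. Take intervention schools of 15, 20 and 20 and control schools of 25, 40 and 40, and move the school of 25. Weight each school by 1/[ICC + (1 − ICC)/m] and let each arm's variance be the reciprocal of its summed weights. At d = 0.454, normal-approximation power goes from 69.0% to 71.5% at ICC 0.01, from 61.5% to 62.7% at 0.02, and from 45.8% to 45.0% at 0.05.

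**The case against.** The strongest defence is that the switch was open and limited. It used the two parameters that had governed the randomisation. It came before baseline measures, so nothing in the text suggests that outcome data prompted it. Families were recruited before randomisation and did not know their arm until the baseline record was complete. The Discussion names the switch as a weakness. All of this stands and makes gross manipulation implausible. It does not make the school's final arm a random assignment, and it does not correct the label.

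A reader might infer that the investigators picked the school freely, by hand. The article does not say who chose it or how; the absence of a described draw is all that can be stated.

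A reader might also infer that the switch reduced power. That holds for equal school sizes only. The worry about the intervention group suggests that this arm may have become small, and then the switch could have helped a little.

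It would also go too far to say that nothing planned addresses bias. Section 2.7 includes baseline intake in the model and adjusts for group imbalances and confounders such as parental education, and Section 2.5 collects data on class closures. These can reduce measured imbalance. They do not show how far the result depends on the one school.

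Finally, a condensed article may leave further sensitivity analyses to a fuller plan. That has some force for the missing analyses taken alone. It has none for the intention-to-treat label or the power rationale, which are printed statements.

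**Conclusion.** The point holds in this form. The primary comparison includes one cluster of six whose arm was changed after a known randomisation, under an intention-to-treat label that does not fit if the changed allocation is used and is ambiguous as written. None of the listed sensitivity analyses isolates that school.

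The power rationale is unsound as worded, but the net effect of the switch on power is undetermined: from a loss of about 5 percentage points with equal schools to a gain of about 2 to 4 points in the small-arm examples, clustering ignored. More firmly, if the implied 24% loss falls on the 160, no split exceeds about 71% before clustering. That shortfall is a sample-size problem under either split and was not caused by the switch. These figures rest on the back-solved d of about 0.45 and on assumed school sizes and ICCs.

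**What to change.** The article describes the trial as ongoing, so the following can be settled before follow-up data are analysed.

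- State how the moved school was chosen, and report the move as a non-random departure from the allocation.
- State that the primary analysis uses the allocation after reassignment, and label it so instead of plain intention-to-treat.
- Replace the power rationale with the achievable power at 4 v 2 schools, using actual school sizes and a range of ICCs.
- Pre-specify two sensitivity analyses of the primary outcome: (a) by the original 3:3 allocation, noting that any effect is diluted because the moved school received the intervention; (b) without the moved school, 3 v 2, noting that this does not fully restore randomisation, since the two remaining controls are those left after a non-random removal.
- Report both beside the main result, with no formal rule that they must agree.
- Tabulate the loss from 237 to 160 by school and original arm.

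The cost is two further model fits, a few table rows and some rewording. The companion estimates will be less precise (b) or diluted (a), and should be read as showing dependence on one school, not as replacement tests.
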